**Assessments:**				
DFIQ			X	X
Managing Needle Distress Questionnaire (MNDQ)		X		X
Blood/ Injection Fear Scale (BIFS)		X	X	X
Hospital Anxiety & Depression Scale (HADS)		X	X	X
Patient INJECT evaluation survey	At the end of 6-week intervention			
INJECT study satisfaction survey	Immediately post the completion of online education program			
Qualitative semi-structured interview study with nurses and patients	Following the completion of the pilot study			

### Qualitative study

At the end of the pilot, we will conduct semi-structured interviews with nurses and patients who participated in the study. Interviews will be conducted by a person not involved in study delivery. Interview questions will explore the acceptability of the intervention, feedback about the conduct of the study, preferences and perspectives on each element of the intervention, and barrier or facilitators to participation or completion. Interviews will be recorded, transcribed verbatim and thematically analysed by the research team using NVivo 12 software [32].

### Sample size

As this is a pilot feasibility study that does not propose inferential tests, power calculation is not essential. Our sample size calculation is based on the pragmatics of recruitment and the necessities for examining feasibility among a broad group of patients. We aim to recruit 25 patients. Allowing for a conservative 25% dropout due to death, illness, transplantation, change in dialysis modality and retention rates, we aim to have 20 patients in total.

### Outcome measures and evaluations

Outcome measures are presented in Table 4. We intend to undertake a thorough process evaluation of each component of the INJECT intervention from both a patient and nurse perspective to obtain a substantial body of feedback about acceptability and feasibility. We anticipate 50% retention rate for patients who are enrolled into the study. We acknowledge that undertaking a self-directed CBT program may not be of interest to all patients with needle fear. Based on previous studies reporting on the use of CBT interventions, dropout rates for psychotherapy range from 16% at the pretreatment phase to 26% at the treatment phase, with some studies reporting an average dropout rate of 47% [35, 36]. Acceptability will be assessed qualitatively, and we anticipate that the intervention will be acceptable from our qualitative approaches. We are unable to put a specific percentage on the reach in this intervention. In our point prevalence survey study, 36% of patients reported needle fear [3]; however, some of them may adapt and will not have an ongoing needle fear. We will use a range of quantitative and qualitative methods including tools to measure needle distress, evaluation surveys and direct interviews to evaluate the experience of patient and nurse participants. Self-devised Patient INJECT evaluation survey and INJECT study satisfaction survey will be pretested with the first 5 patients enrolled in the study. We will capture barriers to recruitment, retention and study completion as well as identify facilitators for successful engagement of nurses and patients. We will record any adverse events to capture safety of the intervention. Participants will have a support from trained dialysis nurses and the Research Officer throughout the study and will be regularly asked about adverse effects as part of the standardised weekly review with the research officer who will be trained to conduct the study. If a patient reports adverse effects, the research officer will discuss this with the participant and with permission, members of the study team. The study team comprises medical and psychology-trained members who will determine the appropriate course of action. The treating nephrologist or the renal psychologist (INJECT investigator) will be involved as appropriate. Finally, we will evaluate clinical outcomes with respect to dialysis vascular access. As this is a feasibility pilot, the assessment of validity or reliability is outside the scope of this study and it will not be assessed.

**Table 4 Tab4:** Outcome measures

Outcome domain	Evaluation measures
Primary outcome	
Patient feasibility/acceptability of the intervention	• Patient INJECT evaluation survey: evaluates the feasibility and acceptance of the intervention, identifies which components were most useful or desired (Additional file 4). Self-devised survey uses a 5-point scale (1 = very unsuccessful, 5 = very successful and 1 = not at all, 5 = a lot). A higher score indicates higher success/acceptance of the intervention. • INJECT study satisfaction survey: assesses satisfaction with the content of the online intervention and the ability to understand and utilise presented learning material (Additional file 5). Self-devised survey uses a 5-point scale (1 = disagree, 5 = agree). A higher score indicates greater satisfaction. • Engagement measures: (i) The reach (i.e. proportion of participants who were approached who then agreed to take part in the study) (ii) Retention rates (iii) Completion rates (iv) Online module metrics and analytics—average time spent on page, time to completion of modules, engagement with comments section of platform (v) Reporting to project officer during the study period Semi-structured interviews with study participants to describe their experiences and preferences
Secondary outcomes	
Measures of needle distress	• Blood/Injection Fear Scale (BIFS) obtains specific information on physiological symptoms of anxiety [33]. The scale measures fear of blood/injection on a 5-point scale (1 = strongly agree, 5 = strongly disagree). Lower score indicates higher level of fear. Chronic disease patients’ data for reliability and validity: Cronbach’s α 0.98 • Managing Needle Distress Questionnaire (MNDQ), a self-devised questionnaire to assess patient’s distress (Additional file 6). Self-devised unvalidated survey measures distress on a 5-point scale (1 = agree, 5 = disagree). A higher score indicates greater distress. • Dialysis Fear of Injection Questionnaire (DFIQ) assesses a change in managing needle distress [9]. It measures fear of injection on a 4-point scale (0 = almost never, 3 = almost always). Renal data for reliability and validity: sensitivity 0.88, specificity 0.72, Cronbach’s α 0.87.
Measure of distress	Hospital Anxiety & Depression Scale (HADS), a standardised tool for measuring anxiety and depression [34]. The scale consists of 2 subscales: anxiety and depression. Each subscale has 7 items with a score of 0 to 21. A higher score indicates greater anxiety/depression. Renal data for reliability and validity: sensitivity 0.81, specificity 0.90, Cronbach’s α 0.85.
Cannulation outcomes (vascular access/clinical outcomes)	• Collected from the hospital electronic system as - Missed cannulations—i.e. missed veins in the initial attempt or subsequent attempt(s) of needling (at each dialysis session for the duration of the study) - Access surgical interventions (at each dialysis session for the duration of the study)
Acceptability and evaluation of nursing education program	Surveys administered before and after the education to evaluate self-rated knowledge about cannulation practices, confidence in managing patients with needle distress, and ability to support patients participating in INJECT. Self-devised unvalidated survey with scores 1 (disagree) to 5 (agree). Higher score indicates greater knowledge/confidence/abilities. Semi-structured interviews with dialysis nurses to describe their experiences and preferences

### Progression criteria

Decision-making about progression to a larger scale evaluation will be based on a process evaluation of recruitment, retention, intervention acceptability and feasibility [37]. Process evaluation will occur at regular intervals throughout the pilot study.If we recruit between 50 and 80% of the target sample, the recruitment strategy will be reviewed to determine the number of patients approached and screened, the number of patients that met eligibility criteria and the number of eligible patients agreeing to participate. Based on the findings, we will establish whether to proceed with a larger evaluation with some minor modifications.If less than 50% of participants are retained in the study, a list of reasons for attrition will be inspected and progression to a larger trial will be reconsidered and the potential intervention reviewed and refined.Outcome data for at least 80% of participants who have completed online education program will be required for the progression to a larger trial.The patient evaluation survey together with exit interviews with patients will provide feedback on each component of the intervention. If the majority of patients find an individual component of the intervention useful (by selecting either agree or strongly agree in the survey), that component will be retained. A lower score will help inform the decision whether some modifications are required, or whether it is realistic to proceed with a component of the intervention.Feedback from qualitative interviews will also assist in optimising the intervention.

These progression criteria will inform the decision about trial conduct and review trial processes in order to decide whether the continuation to the main trial is appropriate.

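### The 80% outcome-data progression criterion counts only participants who finished the online program, and no progression rule covers those who stay in the study without finishing

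*Protocol article*

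**What the plan says.** All references are to the protocol article.

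- **Progression criteria, outcome data:** "Outcome data for at least 80% of participants who have completed online education program will be required for the progression to a larger trial". This is the only numerical rule in the section worded as a requirement.
- **Progression criteria, retention:** "If less than 50% of participants are retained in the study, a list of reasons for attrition will be inspected", after which "progression to a larger trial will be reconsidered and the potential intervention reviewed and refined". The rule is about remaining in the study, and missing it leads to reconsideration.
- **Sample size:** "We aim to recruit 25 patients", and "Allowing for a conservative 25% dropout due to death, illness, transplantation, change in dialysis modality and retention rates, we aim to have 20 patients".
- **Outcome measures and evaluations:** "We anticipate 50% retention rate for patients who are enrolled into the study".
- **Table 3:** the satisfaction survey is timed "Immediately post the completion of online education program". The patient evaluation survey is timed "At the end of 6-week intervention", with no stated condition that the modules be finished.
- **Table 4:** both surveys, reach, retention, completion, module metrics and interviews belong to the primary feasibility and acceptability outcome. Completion is therefore measured, but the Progression criteria section attaches no threshold to it.

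**The concern.** Finishing the modules is itself one of the feasibility results the pilot is meant to produce. A data-completeness criterion that conditions on it has a denominator that shrinks as fewer people finish, so the number of participants who must supply data falls with it. Non-completion alone can never fail the criterion.

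The retention rule closes only part of the gap. A participant who remains in the study but does not finish counts as retained, and is also outside the denominator of the 80% rule. Neither rule registers that person.

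The pilot is intended to guide a larger study, which will need outcomes from everyone enrolled, including people who stop the modules. A criterion limited to completers cannot show whether that is achievable. The satisfaction survey raises a related, smaller issue. It asks about the online content and whether the material could be understood and used, yet people who stop partway have no scheduled occasion to answer it.

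**Working it through.** **Inputs:** 25 to be recruited, 25% dropout and 20 remaining (Sample size); 50% anticipated retention (Outcome measures and evaluations); the 50% retention trigger and the 80% outcome-data rule (Progression criteria).

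**Step 1. The plan's own figure.** 20 × (1 + 0.25) = 25, which matches the stated target. Dividing instead gives 20 / (1 − 0.25) = 26.7, or 27, and working forward gives 25 × 0.75 = 18.75. The differences are within two patients, so 25 recruited and about 20 remaining is reproduced. The other attrition figure gives 25 × 0.50 = 12.5 remaining, which is not close to 20.

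**Step 2. What the 80% rule demands.** With c completers, the smallest passing number is m = 0.8 × c, rounded up. As a share of 25 enrolled:

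| Completers c | 0.8 × c | Minimum m | m / 25 |
|---|---|---|---|
| 25 | 20 | 20 | 80% |
| 19 | 15.2 | 16 | 64% |
| 13 | 10.4 | 11 | 44% |
| 10 | 8 | 8 | 32% |
| 5 | 4 | 4 | 16% |

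**Step 3. Adding the retention rule.** The smallest whole number of 25 that is not below 50% is 13 (13/25 = 52%).

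- 13 retained and all 13 finish: 11 with data are enough, 11/25 = 44%.
- 13 retained and 10 finish: 8 with data are enough, 8/25 = 32%.
- Limiting illustration, not a forecast: all 25 retained and 5 finish. The retention rule is fully met and 4 with data satisfy the 80% rule, 4/25 = 16%.

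Recruitment is at target in all three cases, so the recruitment review is not triggered. Each m is what the rules require, not a prediction of what will be collected.

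**Step 4. Changing the denominator but keeping 80%.** The requirement becomes 0.8 × 25 = 20 participants with data. If each participant independently has probability p of providing data, X is Binomial(25, p) and the chance of passing is P(X ≥ 20):

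| p | P(X ≥ 20) |
|---|---|
| 0.50 (anticipated retention) | 0.002 |
| 0.75 (sample-size dropout) | 0.378 |
| 0.80 | 0.617 |

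The denominator and the threshold therefore have to be changed together.

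**The case against.** The strongest reply is that the rules should be read as a set. Attrition has its own criterion immediately before the 80% rule, the 80% rule is a necessary condition rather than a sufficient one, and the section says the criteria inform a decision. That is correct. A reader might infer that heavy dropout cannot affect progression at all, but the text does not support this: retention below 50% prompts an inspection of reasons and reconsideration. What remains is the group that stays in the study without finishing, which neither rule counts.

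A reader might also infer that acceptability is measured only among completers. The documents do not say so. The evaluation survey is tied to the end of the six weeks, and the Qualitative study section plans interviews with patients who took part, including questions on barriers to completion. The rule for keeping a component relies on the evaluation survey and exit interviews, not the satisfaction survey. A week-6 survey may in practice miss early dropouts, but it is not restricted to completers. Asking about content after it has been seen is also defensible. Upward bias in satisfaction is plausible but not shown, since the Sample size section also lists death, illness, transplantation and change of modality as reasons for leaving.

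Third, low recruitment might be added to make a more extreme case that passes everything. Recruiting 13 of 25 (52%) falls in the 50 to 80% band, which triggers a review, so it is not a pass.

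Finally, the 44% and 32% are floors. More completers than the minimum may give data, retained non-completers may also be assessed, and the Data collection section says data gathered before withdrawal will be used. The Table 3 column headings, as extracted, do not settle whether the follow-up questionnaires depend on finishing the modules.

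**Conclusion.** The point holds in a limited form. The one progression rule phrased as a numerical requirement is conditioned on finishing the program, no rule sets a completion level, and retained non-completers are covered by neither the outcome-data rule nor the retention rule. At full recruitment with 13 retained, both rules can be met with outcome data required on as few as 11/25 (44%) or 8/25 (32%) of those enrolled, depending on whether 13 or 10 finish. These counts assume 25 enrolled and only the minimum data the rules demand. The binomial figures further assume independent participants with a common probability of providing data.

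The satisfaction survey lacks a time point for non-completers, but it is one of several acceptability measures and feeds no progression rule. In a 25-patient feasibility study with a discretionary progression decision, this is a moderate correction to make before that decision is taken. It does not undermine the pilot as a whole.

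**What to change.** 1. **Outcome-data criterion.** Define it as the percentage of all enrolled participants (consented, DFIQ ≥ 2) with 6-week DFIQ, BIFS, HADS and MNDQ data, whether or not the modules were finished. Report the percentage among completers as descriptive.
2. **Threshold.** First reconcile the 25% dropout figure in Sample size with the 50% retention figure in Outcome measures and evaluations, then set the required percentage to match. Carrying 80% over unchanged is not realistic at 50% retention.
3. **Satisfaction survey.** Offer it to every enrolled participant at program completion or week 6, whichever comes first, with an option for those who did not finish.

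The cost is revised protocol wording and a few additional questionnaires, which the research officer's existing weekly contact can carry. The reported percentage will be lower than the completer figure, but it will describe what a larger trial needs to know.

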### Planned statistical analysis

Descriptive statistics will be employed to describe the cohort demographic and to analyse survey responses. Qualitative survey data (i.e. responses to open-ended questions) will be extracted using narrative synthesis. Reasons for ineligibility and for non-participation will be reported. Data collected from the DFIQ, MNDQ, BIFS and HADS questionnaires will be analysed by Wilcoxon matched pairs signed-rank tests (Stata software) to calculate changes in scores over the study data collection time points.

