### Data collection

At the enrolment, informed consent and demographic data will be collected. Demographic questionnaire is listed in Additional file 3. A schedule for enrolment, intervention and assessments is displayed as per SPIRIT guidelines in Table 3. Data collected prior to participant’s withdrawal will be used in de-identified form for group analysis and reporting. Course analytics from the online learning platform will enable tracking of patients’ learning and progress through the modules.

**Table 3 Tab3:** Schedule of enrolment, intervention and assessments

	Study period			
	Enrolment	Baseline	3 weeks	6 weeks
		psychological assessment	Post education program completion	
**Timepoint**	**-** ***t***_**1**_	***t***_**0**_	***t***_**1**_	***t***_**2**_

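### Matched-pairs tests confine the week-6 change in distress scores to completers, about 12–13 of 25 patients at the anticipated retention, and the result may be biased if leaving is related to distress or benefit

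*Protocol article*

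**What the plan says.** The Planned statistical analysis section gives one method for change on DFIQ, MNDQ, BIFS and HADS: scores "will be analysed by Wilcoxon matched pairs signed-rank tests (Stata software) to calculate changes in scores over the study data collection time points".

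Table 3 sets the assessment times:
- DFIQ: enrolment screen, week 3 and week 6.
- BIFS and HADS: baseline, week 3 and week 6.
- MNDQ: baseline and week 6 only.

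Two attrition figures appear. Under Sample size: "We aim to recruit 25 patients", then "Allowing for a conservative 25% dropout due to death, illness, transplantation, change in dialysis modality and retention rates, we aim to have 20 patients". Under Outcome measures and evaluations: "We anticipate 50% retention rate for patients who are enrolled into the study". The latter section adds that "undertaking a self-directed CBT program may not be of interest to all patients with needle fear".

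The Data collection section says that data gathered before a participant's "withdrawal will be used in de-identified form for group analysis and reporting".

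The abstract calls the secondary outcomes exploratory. The Progression criteria section relies on recruitment, retention, completeness of outcome data and acceptability, not on score change.

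**The concern.** A signed-rank test on pairs needs a first and a later score from the same patient. Anyone without a week-6 score is absent from every contrast that ends at week 6. For MNDQ, which has no week-3 assessment, that patient contributes to no change at all. For the other three instruments, the contrasts to week 3 and to week 6 would rest on different sets of patients.

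This matters if those who leave differ from those who stay in how their distress changes. The protocol itself foresees that some patients will not take to a self-directed programme, and its Discussion says that the intervention depends on high patient activation. Selective retention of engaged patients is therefore plausible. There is no control arm to expose it. The 80% outcome-data criterion would not reveal it either, because its denominator is patients who completed the online programme. The abstract's conclusion says that the results will inform larger trials, so a change that describes stayers only could mislead that planning.

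**Working it through.** **Inputs from the protocol.** Target n = 25; dropout 25% with 20 patients aimed for (Sample size); retention 50% (Outcome measures and evaluations); assessment times (Table 3).

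**Assumptions, not in the protocol.** A patient who leaves has no week-6 score. Change is standardised to mean 0 and SD 1 in all enrolled patients, with positive values meaning improvement. The test is two-sided at 5%. The correlation r between staying and improving is varied, since the protocol gives nothing from which to estimate it.

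**1. The plan's own figure.** 25 × (1 − 0.25) = 18.75, or about 19, against the stated 20. This agrees within rounding of a pragmatic target; exactly 20 of 25 would be 20% dropout.

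**2. Pairs available at week 6.**
- 50% retention: 25 × 0.50 = 12.5, so 12 or 13 pairs.
- 25% dropout: about 19 pairs.
- If each patient stays with probability 0.5, the chance of keeping 20 or more of 25 is about 0.2%. The two planning figures are not interchangeable.

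**3. Bias in general form.** Completers-only bias = (1 − retention) × (mean change in stayers − mean change in leavers). For an assumed stayer-minus-leaver gap of −0.5 / 0 / 0.5 / 1.0 SD:
- 50% retention: −0.25 / 0 / 0.25 / 0.50 SD.
- 75% retention: −0.125 / 0 / 0.125 / 0.25 SD.

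**4. The same in terms of a correlation.** Let a patient stay when a latent normal variable, correlated r with change, exceeds the cut c that gives the stated retention. The mean change in stayers is then r × φ(c) / retention. The multiplier φ(c) / retention is 0.798 at 50% retention and 0.424 at 75%. Rejection rates come from simulating the Wilcoxon test with n = 25 and no true change.

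| r (assumed) | Mean change, 50% retained | Rejection | Mean change, 75% retained | Rejection |
|---|---|---|---|---|
| −0.3 | −0.24 SD | 11% | −0.12 to −0.13 SD | 8% |
| 0 | 0 | 5% | 0 | about 5% |
| 0.3 | 0.24 SD | 11–12% | 0.13 SD | 7% |
| 0.5 | 0.40 SD | 27% | 0.21–0.22 SD | 14–15% |
| 0.7 | 0.56 SD | 54% | 0.29–0.30 SD | 25% |

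**5. What an all-available-data estimate would recover.** If leaving depends only on baseline or week-3 scores that were observed, such an estimate removes the bias. If leaving depends on the unseen final change, as in step 4, it does not. With 50% retention and r = 0.3 / 0.5 / 0.7:
- Leavers have only a baseline score, unrelated to change: 0.24 / 0.40 / 0.56 SD, no gain. MNDQ is in this position for every leaver.
- Every leaver has a week-3 change correlated q = 0.5 with final change (assumed): 0.18 / 0.31 / 0.45 SD.
- Worked case, r = 0.5: the variance-reduction factor at 50% retention is 0.6366. The slope of final on week-3 change in stayers is (0.5 − 0.125 × 0.6366) / (1 − 0.0625 × 0.6366) = 0.438. The estimate is 0.399 − 0.438 × 0.1995 = 0.31 SD.
- With q = 0.6 instead, r = 0.5 gives 0.27 SD.

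**The case against.** The strongest reply is that this is an exploratory analysis in a feasibility pilot. The protocol disclaims inferential comparisons, states no significance level, and makes no progression decision on score change. A signed-rank test is reasonable for small-sample ordinal scores, and missing-data handling commonly sits in an analysis plan that is not shown. Most of this stands. It limits the consequence, and the rejection rates above correspond to no decision in the plan. It does not remove the point, because the matched-pairs method is stated, not left open.

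Three stronger readings are tempting, and the document supports none of them.

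- **That the reported change is biased towards improvement.** A reader might infer this from the remark about lack of interest in CBT. But lack of interest is not failure to benefit, and the protocol also lists "dropout due to death, illness, transplantation, change in dialysis modality and retention rates", several of which need not track change in needle distress. Bias is zero if leaving is unrelated to change, and reverses if improved patients stop early.
- **That half the cohort vanishes from the distress results.** Half is one of two conflicting figures. Patients who leave after week 3 still give a pair to week 3 on DFIQ, BIFS and HADS; only MNDQ lacks one.
- **That the Data collection section is contradicted.** It says that data collected before withdrawal "will be used in de-identified form for group analysis and reporting". Cohort description, module metrics, retention rates and week-3 pairs all use such data. The sentence does not promise that every score enters every change test, so there is a tension with the named test but no breach.

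**Conclusion.** The point holds as a limited one. On the protocol's own figures, change from first score to week 6 will describe about 12–13 of 25 patients at 50% retention, or about 19 at 25% dropout, provided that leavers have no week-6 score. Whether that subset misleads depends on why patients leave. If staying goes with improving, which is the most plausible direction, correlations of 0.3 to 0.7 would produce an apparent gain of 0.24–0.56 SD at 50% retention and 0.13–0.30 SD at 75%, with no true change. These correlations are assumptions. Neither the sign nor the size of any bias can be read from the protocol, and no bias at all is among the possibilities. What is at stake is how the exploratory change is interpreted when the larger trial is planned, not the decision to progress.

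**What to change.** In the Planned statistical analysis section:
1. Keep the Wilcoxon result, label it completers-only, and give the number of pairs for each contrast.
2. Compare baseline scores (enrolment scores for DFIQ) of leavers and stayers.
3. As a sensitivity analysis, add a repeated-measures estimate of change using every available score: enrolment or baseline, week 3 and week 6.
4. Show the proportion of all enrolled patients who improved, counting a missing week-6 score as not improved, only as a conservative bound. It treats deaths and transplants as failures and so leans the other way.

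Separately, reconcile the 50% retention with the 25% dropout.

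The cost is a few sentences and a little more analysis, with no new patients or data. The model estimates will be imprecise at n = 25, MNDQ gains little because it has no week-3 score, and protection is only partial if leaving depends on change that was never observed.

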## Methods

### Study design

The INJECT study is a single-arm, open-label, non-randomised feasibility pilot that will assess a multifaceted intervention to improve needle distress in HD patients. The study intervention components are shown in Fig. 1:Psychologist review (an overall psychologist assessment, completion of baseline questionnaire and explanation of CBT principles + introduction to VR)Patient self-management program (online CBT education modules with an option to use VR as distraction and support from the research officer)Nursing program (nurse education about needle distress and ways to support patients with their self-management).

A suite of novel strategies forms this entire intervention. Each of the components was chosen and developed based on extensive nursing and patient input and will respectively be tested and evaluated. No control group will be employed in this pilot study because there are no inferential comparisons to be conducted. The study flow is presented in Fig. 2.

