**Enrolment:**				
Informed consent	X			
Eligibility screen- Dialysis Fear of Injection Questionnaire (DFIQ)	X			
Demographics	X			
**Intervention** (6-week duration starting from baseline)				

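### The article gives the absence of inferential tests as its reason for having no control group and no power calculation, yet plans signed-rank tests on four questionnaires

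*Protocol article*

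**What the plan says.** Three sections of the protocol article bear on this.

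- Study design: "No control group will be employed in this pilot study because there are no inferential comparisons to be conducted".
- Sample size: "As this is a pilot feasibility study that does not propose inferential tests, power calculation is not essential". The target of 25 patients is then based on what recruitment allows and on what is needed to examine feasibility.
- Planned statistical analysis: data from the DFIQ, MNDQ, BIFS and HADS "will be analysed by Wilcoxon matched pairs signed-rank tests (Stata software) to calculate changes in scores over the study data collection time points". No pair of time points is singled out, and the section does not call these tests exploratory.

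Table 3 places the DFIQ at enrolment, 3 weeks and 6 weeks; the BIFS and HADS at baseline, 3 weeks and 6 weeks; and the MNDQ at baseline and 6 weeks. Table 4 lists all four as secondary outcomes and describes the HADS as having two subscales. The abstract calls the secondary outcomes exploratory.

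**The concern.** The signed-rank test is inferential: it tests whether paired differences are centred on zero and returns a P value. Planning it on four scales contradicts the premise that the article gives for two design decisions. An unseen analysis plan cannot remove the conflict. If it kept the tests it would contradict Study design and Sample size; if it dropped them it would contradict Planned statistical analysis.

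The sentence also gives the test a job that it does not do by itself. The stated purpose is "to calculate changes in scores over the study data collection time points", but the size of a change comes from an estimate, with an interval for its precision. A larger trial would be designed from those estimates.

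At stake is how the secondary results can be read. They are before-after comparisons without a comparator, over several scales and time points. For the DFIQ, the starting value is the score that admitted the patient.

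**Working it through.** **1. The plan's own figure.** There is no power, alpha or effect size to reproduce. The stated target is 25 recruited and 20 remaining after 25% dropout; 25 × 0.75 = 18.75, close to the stated 20. The contradiction does not depend on these figures.

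**2. The statements side by side.** Study design: no inferential comparisons, therefore no control group. Sample size: no inferential tests, therefore no power calculation. Planned statistical analysis: signed-rank tests on four questionnaires. The third statement denies the premise of the first two.

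**3. How many tests.** The counts follow from the time points in Table 3. A scale measured k times gives 1 first-versus-last contrast, k − 1 contrasts against the first measurement, and k(k − 1)/2 pairwise contrasts.

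| Scale | Time points | First v last | Each later v first | All pairs |
|---|---|---|---|---|
| DFIQ | 3 | 1 | 2 | 3 |
| MNDQ | 2 | 1 | 1 | 1 |
| BIFS | 3 | 1 | 2 | 3 |
| HADS, one score | 3 | 1 | 2 | 3 |
| **Total** | | **4** | **7** | **10** |
| **Total, HADS as two subscales** | | **5** | **9** | **13** |

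**4. Chance of at least one false positive.** Assume alpha 0.05 per test, independent tests and no true change on any scale. The article states none of these. The formula is 1 − 0.95^m for m tests.

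- m = 4: 1 − 0.95^4 = 0.186
- m = 9: 1 − 0.95^9 = 0.370
- m = 10: 1 − 0.95^10 = 0.401
- m = 13: 1 − 0.95^13 = 0.487

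The range is about 19% to 49%. The scales measure related things in the same patients, so the tests are likely to be positively correlated and the true figures lower.

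**5. The DFIQ.** Patients enter only with a DFIQ score of at least 2 (Table 1). Table 3 marks the DFIQ at enrolment as the eligibility screen and then not again until 3 weeks; the baseline column is empty for it. The screening score must therefore be the starting point for any DFIQ change. Scores that cleared a lower limit tend to fall on re-measurement, and with no control group such a fall cannot be told apart from an effect. The article gives neither a total score range nor a distribution, so the size of this cannot be calculated.

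**6. What depends on the tests.** The primary outcomes in Table 4 are surveys, engagement measures and interviews. The Progression criteria section uses recruitment, retention, completeness of outcome data, perceived usefulness and interviews. No questionnaire P value enters either.

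**The case against.** The strongest reply is that nothing in this pilot turns on these tests. The primary aim is feasibility and acceptability, the progression rules ignore the questionnaire results, and the abstract already calls the secondary outcomes exploratory. A pilot may properly omit a power calculation, and the target of 25 rests on pragmatic and feasibility grounds that remain valid with or without tests. All of this stands. It limits the severity but does not reconcile the three statements.

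A reader might infer several stronger things that the document does not support.

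- *The tests will be uncorrected for multiplicity.* The article is silent, and this is commonly left to the analysis plan.
- *The size, spread and precision of change will not be reported.* The article does not say so. It names only a test for these scales, but it also states an intention to calculate changes.
- *The sample size is undermined.* Only the reason given for omitting a power calculation is affected.
- *The patients are selected for high fear.* A threshold of 2 cannot be called high without the total range or distribution.
- *The P values will be presented as efficacy.* No efficacy hypothesis is attached to them; misreading is a risk, not a plan.

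One further objection is correct and shapes the remedy. A confidence interval for the median paired change is itself inferential; the Hodges-Lehmann interval comes from inverting the signed-rank test. Replacing tests with intervals would still leave the claim of no inferential comparisons inaccurate, so the two justifications need rewording under either remedy.

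**Conclusion.** The contradiction is real and lies within the article. Study design and Sample size rest on there being no inferential tests, and Planned statistical analysis specifies them. The test named is also not, by itself, a way to obtain the size of a change.

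The possible multiplicity runs from 4 to 13 tests, or about 19% to 49% for at least one false positive. This rests on an assumed alpha of 0.05, independence and no true change, so it is an illustration that correlation would lower. Regression to the mean on the DFIQ is a further exposure whose size cannot be judged from the document.

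Severity is moderate. The feasibility conclusions and the decision on a larger trial do not depend on these tests, and the recruitment target needs no change.

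**What to change.** **Planned statistical analysis.** Replace the sentence on the four questionnaires with wording such as: *For each scale we will report the median (IQR) at each time point, the median paired change with its 95% confidence interval, the spread of the paired changes, and the number of pairs out of all patients enrolled. These are exploratory estimates; no hypothesis tests will be done and no claim of efficacy will be made.*

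**Study design and Sample size.** Replace the statements about inference with wording such as: *No efficacy hypothesis is tested, and the sample size rests on feasibility.* This remains accurate when confidence intervals are reported.

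**If the tests are kept.** Name the contrasts for each scale, say whether the HADS subscales are tested separately, label the tests exploratory, and correct Study design and Sample size to acknowledge them.

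The cost is one sentence of analysis text and two reworded justifications. No additional data, visits or patients are needed, and no information is lost.
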